### Outcome analysis

Data will be entered in EpiData version 3.1. The statistical software STATA will be used for data analysis. Ratio-scaled data from both groups (intervention and control) will be compared by using parametric methods if data are normally distributed, and if not, nonparametric methods will be used. Nominal scale data will be compared by Chi-square test or by a 95% confidence interval when comparative measures. Categorical variables will be compared using the Pearson´s chi-square test and the Mann–Whitney test, and two-sided level of significance p < 0.05, if it is found optimal. For continuous data changes within the groups will be analysed by using a paired t-test. P < 0.05 will be considered as being statistically significant. Due to the repeated measures a logistic regression analysis will be performed.

All patients will be analysed in the groups to which they are randomly allocated according to intention to treat analysis. This analysis is primarily based on imputation of outcomes by carrying the last known outcome status forward and is supplemented by sensitivity analysis to examine the effect on the results.

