### Secondary outcomes

Secondary analysis will assess the effect of telephone follow-up in the intervention group compared to the control group by change in pain and stiffness scores in WOMAC LK 3.1 Index, change in health-related quality of life measured by the Medical Outcomes Study Short Form (SF-36) [27], change in the General Self-Efficacy Scale score [28], and the number of acute visits to the orthopaedic outpatient clinic.

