### Randomization and blinding

Patients are randomized 1:1 to the intervention group or the control group respectively. The randomization is performed centrally by a web-based randomization program and in blocks unknown to the investigator and other subjects involved in the study. The randomization is executed just before discharge of the patients from hospital.

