### Outcome measures

Outcome measures are collected at baseline defined by 3 days after discharge from hospital, and 1, 3, 6 and 12 months post-surgery. These data are obtained by self-administered questionnaires mailed to the patients, except for the questionnaire for baseline data, as the first questionnaires are handed to the patients just before discharge. The patients are contacted by phone once by research assistants if questionnaires are not received by the researcher 7 days after scheduled date for answering.

It is recommended to use a disease-specific health status measure supplemented by a generic measure of health-related quality of life to fully assess outcomes after TKA [32]. A combination of the WOMAC Index and SF-36 is the most frequently used combination [4] and will be used in this trial. Self-efficacy will be measured by the General Self-Efficacy Scale.

All questionnaires are validated and available in a Danish version.

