### Data collection

From the medical records the following data are collected: age, gender, marital status, body mass index, ASA-group (American Society of Anesthesiologist physical status classification), co-morbidities, length of stay, and the code for the surgical intervention.

Further, the following patient-reported data are collected: level of education, occupational status, home care and nursing care at home, and inhibited physical function not caused by the TKA.

Additional patient-reported data about participation in the rehabilitation program, readmissions, and unscheduled contact with healthcare professionals (general practitioner, readmission and emergency department, doctor on call, the orthopaedic ward or the orthopaedic outpatient clinic) are collected as control for confounders.

Additionally, qualitative and quantitative data from the telephone follow-up consultations are documented in regard to duration as well as identified health problems and provided counselling related to the predefined themes structuring the intervention.

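### The between-arm comparison is valid, but its test depends on a normality check, it names no use of the baseline score, and within-arm paired t-tests are added that cannot isolate the intervention effect

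*Protocol article*

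**What the plan says.** Three statements in the Outcome analysis section of the protocol article matter here.

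- Between arms, ratio-scaled data "will be compared by using parametric methods if data are normally distributed, and if not, nonparametric methods will be used".
- Within arms: "For continuous data changes within the groups will be analysed by using a paired t-test".
- The only model named: "Due to the repeated measures a logistic regression analysis will be performed". No covariates are listed for it.

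The Primary outcome and Sample size sections set the criterion as a difference of at least 12 points in WOMAC physical function between intervention and control. The Secondary outcomes section defines the WOMAC pain and stiffness, SF-36 and self-efficacy outcomes as change (for example "change in the General Self-Efficacy Scale score"), compared between the arms.

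On baseline, the Outcome measures section says: "Outcome measures are collected at baseline defined by 3 days after discharge from hospital, and 1, 3, 6 and 12 months post-surgery". The Randomization and blinding section says: "The randomization is executed just before discharge of the patients from hospital". Under Data collection, the items that "are collected as control for confounders" are rehabilitation participation, readmissions and unscheduled contacts. The baseline outcome score is not among them.

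**The concern.** The trial's question is a difference between arms, in points. Three stated choices serve that question poorly.

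1. **The effect measure is left to the data.** A t-test comes with a mean difference that can be read against 12 points. A rank test does not. Which one is reported depends on the distribution observed.
2. **The baseline score plays no named part in the comparison.** It is collected on every outcome questionnaire, yet no between-arm analysis is said to use it. Precision available at almost no cost is given up.
3. **The paired t-tests answer another question.** Baseline falls a few days after surgery, so change from it contains recovery in both arms. In the intervention arm it is recovery plus any effect, and a within-arm test cannot separate the two.

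At stake are precision, a clear effect measure and safe interpretation. The validity of the randomised comparison is not in question.

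**Working it through.** **Inputs from the article.** Difference 12 points, SD 18, α = 5%, power 90%, 48 per arm before dropout, 20% dropout, 58 per arm randomised (Sample size). Two-sided testing (Outcome analysis). Expected mean of 32 at 6 months on a 0–100 scale, with room for a 12-point improvement (WOMAC Index LK 3.1). **Assumed:** the baseline to follow-up correlation r, which the article does not give.

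**The plan's own figure.** n per arm = 2(1.960 + 1.282)² × 18² / 12² = 47.3, rounded up to 48. This matches. The sizing is that of an unadjusted two-sided comparison of two means.

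**Evaluable patients.** 58 × 0.8 = 46.4, so 46 per arm with an observed outcome at the stated dropout.

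**Effect of baseline adjustment.** Residual SD = 18√(1 − r²). Standard error = SD × √(2/46). Power is from the noncentral t with 90 degrees of freedom (the one degree lost to the covariate is ignored). The last column compares raw change scores instead, with SD = 18√(2(1 − r)), taking the same SD at both times.

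| r (assumed) | Variance cut by adjustment | Adjusted SD | SE, 46 per arm | Power, adjusted | Power, change scores |
|---|---|---|---|---|---|
| unadjusted | – | 18.0 | 3.75 | 88.6% | – |
| 0.1 | 1% | 17.9 | 3.73 | 88.9% | 65.5% |
| 0.2 | 4% | 17.6 | 3.68 | 89.8% | 70.6% |
| 0.3 | 9% | 17.2 | 3.58 | 91.2% | 76.2% |
| 0.4 | 16% | 16.5 | 3.44 | 93.2% | 82.3% |
| 0.5 | 25% | 15.6 | 3.25 | 95.5% | 88.6% |
| 0.6 | 36% | 14.4 | 3.00 | 97.7% | 94.3% |

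The change-score comparison is less precise than the adjusted one throughout this range. It is also less precise than the follow-up score alone when r is below 0.5.

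**Is a switch to a rank test realistic?** With mean 32 − 12 = 20 and SD 18, a normal curve would put Φ(−20/18) = 13.3% of values below the scale's floor of zero. With mean 32 the share is Φ(−32/18) = 3.8%. Some skewness in the better arm is therefore plausible under the planning figures.

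**Does the switch harm the error rate?** In a simulation with 48 per arm and 3,000 trials per setting, normality was tested in each arm. Type I error was 5.1% for normal data and 4.8% for skewed (gamma) data. It does not.

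**What the paired tests show when there is no treatment effect.** Take 48 per arm, the same true mean change m in both arms, change SD = 18√(2(1 − r)) and noncentrality m√48 / SD. If p is the chance of significance in one arm, the arms disagree with probability 2p(1 − p).

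| Common change m | r | p per arm | Arms disagree |
|---|---|---|---|
| 20 points | 0.3 to 0.7 | about 100% | about 0% |
| 5 points | 0.3 | 35.7% | 45.9% |
| 5 points | 0.5 | 47.0% | 49.8% |
| 5 points | 0.7 | 68.2% | 43.4% |

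With a large common recovery both arms are significant. With a small one the arms often disagree. Neither pattern says anything about the intervention.

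**The case against.** A good deal can be said for the plan, and most of it stands.

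- **The paired tests do not replace the between-arm test.** A reader might infer that one arm's p-value will be set against the other's. Nothing says so: the Aim, the outcome sections and the first analysis sentence all frame the effect as intervention against control. The between-arm sentence can also be read to cover change scores.
- **Both arms need not come out significant.** The p < 0.001 in the WOMAC section concerns WOMAC subscales at 3 and 6 months. It says nothing about self-efficacy, and a common 5-point change is significant in only 36–68% of cases per arm.
- **There is no validity failure.** A reader might infer bias or an inflated error rate. The unadjusted randomised comparison is unbiased, the 48 per arm fits it, and the simulated type I error stays near 5%. On the skewed data simulated, the switch even raised power (96.0% against 89.6% for the t-test).
- **The gain may be small.** Baseline is an early postoperative score and follow-up runs to 12 months, so r could be low. At r = 0.1–0.2 adjustment adds about one percentage point or less. The 46 per arm is also a choice: the plan carries last values forward for all randomised patients, and at 58 per arm unadjusted power is 94.5% if the SD stays at 18.
- **Covariates are often left to a fuller document.** This is fair as to detail, and adjustment may be specified there. But the data-dependent test and the paired t-tests are choices stated here, and a later document would have to reverse them.

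What remains is that the 12-point criterion needs a mean difference that the stated rule does not guarantee, that the baseline score has no named use between arms, and that the paired tests carry no evidence of effect.

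**Conclusion.** The point holds as one of efficiency and clarity, worth changing but not invalidating. The planned between-arm test is valid, and the sample size is right for it before dropout. The stated rule could leave the primary result without the mean difference that the 12-point criterion requires, and the within-arm tests cannot separate the intervention from recovery.

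The direction of the precision loss is certain for any non-zero correlation, but its size is not. With 46 per arm, power moves from 88.6% to about 89–90% at r = 0.1–0.2 and to 91–98% at r = 0.3–0.6. These figures rest on an assumed r, SD 18 and a true difference of 12 points.

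**What to change.** For each continuous outcome, pre-specify one primary estimate: the between-arm mean difference with 95% CI from a linear (mixed) model adjusted for that outcome's baseline score. Use it whatever a normality check shows, with robust or bootstrap intervals if the data are skewed, and keep a rank test as sensitivity only. Report within-arm changes descriptively, without treating their p-values as evidence of effect.

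The baseline needs a rule of its own. It is due 3 days after discharge, which is after un-blinded randomisation and one day before the first call. Excluding baselines completed after the first call would not do, because controls receive no call and only one arm would lose data. Apply the same cut-off to both arms (for example, completed by day 3 after discharge). Treat later or absent baselines as missing by a method that keeps all randomised patients, and report an unadjusted analysis as sensitivity.

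The cost is a little more analysis work and reliance on recorded completion dates, which the article does not say are kept. The baseline score is already collected, and the article reports recruitment at 50%, so the wording can be settled before outcomes are analysed.

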### Primary outcome

In a 12 months period the effect of telephone follow-up is primarily assessed by a significant improvement of ≥ 12 points for the physical function score in the intervention group compared to the control group measured by the disease-specific Western Ontario and McMaster Universities Osteoarthritis (WOMAC) LK 3.1 Index [26].

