### WOMAC Index LK 3.1

WOMAC is developed and recommended for evaluation of treatment effect of TKA [26,32]. The WOMAC Index includes 3 subscales: pain (7 items), stiffness (2 items) and physical function (17 items). The Likert scale version of the index will be used with the following description for all items: none, mild, moderate, severe, or extreme - corresponding to an ordinal scale of 0–4. The score in each subscale is standardized to a score of 0 to 100 with higher scores indicating more pain, stiffness and functional limitations.

Patients with osteoarthritis in the knee were involved during the development of the item inventory of the index in order to assess clinical relevance [26]. In comparison with several other instruments used to evaluate the consequences of osteoarthritis and generic measurements of health-related quality of life [26,32,33] the WOMAC Index has shown adequate properties in regard to validity.

The original, as well as European WOMAC Index Likert scale versions, have been tested as a patient completed questionnaire on TKA-patients pre- and post-surgery, presenting acceptable reliability concerning values for internal consistency (Crohnbach´s alpha y for pain .78 - .93; stiffness .75 - .93 and physical function .92 - .98) [26,34-36], and a test-retest reliability assessed by the intra-class correlation (pain .78 - 95, stiffness .67 - .90 and physical function .71 - .92) [34-36]. The ceiling and floor effect post-surgery were under 15% 6 months post-surgery, except for a ceiling effect at 15.79 for stiffness [37].

The responsiveness has been documented in several studies, and the mean changes at follow-ups 3 and 6 months post TKA-surgery were significant (p < 0.001) for all subscales [26,32,35].

The mean score of the subscale physical function 6 month post-surgery is estimated to 32 based on scores presented in the literature [38], allowing an improvement of 12 points as hypothesized.

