### Sample size

Calculation of the sample size is based on the primary outcome physical function in the WOMAC Index based on the smallest clinically relevant improvement, which is reported to 5.3, 11.8 and 20.4 points related to low, intermediate and high baseline score tertiles respectively [42]. A difference of a minimum of 12 points in favour of the intervention group compared to the control group during a period of 12 months post-surgery is assessed as a clinical relevant outcome in this trial and determined as basis for estimation of the sample size. The standard deviation for the entire population is estimated to 18 points. Sample size is calculated with the assumption of normally distributed data with α = 5% and 1-β = 90% and an equal number of patients in each group. It is estimated that 48 patients are needed in each group. With an expected drop out rate of 20% 58 patients have to be included in each group.

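### The only analysis named for the repeated measures is logistic regression, which does not fit a 0-100 score sized on a mean difference; the deciding analysis and visit are not fixed

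*Protocol article*

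**What the plan says.** The primary outcome is WOMAC physical function. Under WOMAC Index LK 3.1: "The score in each subscale is standardized to a score of 0 to 100 with higher scores indicating more pain, stiffness and functional limitations". Under Primary outcome, the effect over 12 months is "primarily assessed by a significant improvement of ≥ 12 points for the physical function score in the intervention group compared to the control group". Under Outcome measures: "Outcome measures are collected at baseline defined by 3 days after discharge from hospital, and 1, 3, 6 and 12 months post-surgery".

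Under Sample size, the 12-point difference is combined with an SD of 18, α = 5% and 90% power, and "Sample size is calculated with the assumption of normally distributed data". The result is 48 per group, raised to 58 for 20% dropout.

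The Outcome analysis section names three analyses that could bear on such a score:

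- Between groups, ratio-scaled data "will be compared by using parametric methods if data are normally distributed, and if not, nonparametric methods will be used".
- Within groups: "For continuous data changes within the groups will be analysed by using a paired t-test".
- For the longitudinal structure: "Due to the repeated measures a logistic regression analysis will be performed".

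The section also specifies intention to treat, based primarily on last-value-carried-forward imputation with supplementary sensitivity analysis.

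**The concern.** The logistic regression sentence does not match the data it is meant for. WOMAC physical function, pain and stiffness, the SF-36 scales and the self-efficacy total are all scores, and acute visits are a count. The article defines no binary endpoint, responder rule or cut-point. The stated reason is also wrong. Repeated measures call for a model of within-patient correlation. Ordinary logistic regression has none, and no GEE or random-effects version is named.

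This is not detail left to a fuller plan: the article names a method and gives a reason for it, and neither suits the outcome. An analysis plan that followed the sentence would inherit the problem, and one that did not would contradict the published protocol.

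Three things are at stake. An odds ratio cannot show whether a 12-point difference was reached. A cut-point left open in an un-blinded trial could be chosen after the data are seen. Power or error control could also be lost, depending on how the sentence is carried out.

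**Working it through.** **1. Which test is the trial sized for?** Inputs from Sample size: difference 12, SD 18, α = 0.05, power 0.90. I take the test as two-sided; the Sample size section does not say, but Outcome analysis mentions a two-sided level for categorical variables.

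n per group = 2 × (1.960 + 1.282)² × 18² / 12² = 2 × 10.51 × 2.25 = 47.3, so 48. This is the stated figure exactly. (One-sided gives 39; the t-test version gives 48.3.) Power at 48 is Φ(12 / (18 × √(2/48)) − 1.96) = Φ(3.27 − 1.96) = 0.904. The powered test is therefore a two-group comparison of means at one time point, not a logistic regression.

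**2. Which planned analysis matches it?**

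- The parametric group comparison matches, if applied at one visit.
- The paired t-test does not compare the groups.
- The logistic regression neither estimates a mean difference nor models the correlation.

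No visit is fixed. Primary outcome and Sample size speak of a 12-month period. The WOMAC section uses an expected 6-month mean of 32 to argue that 12 points is attainable. The Discussion expects the effect to be strongest in early recovery.

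**3. Illustration: dichotomising at one visit.** Assumptions: normal data, SD 18, control mean 32 (the article's 6-month figure), intervention mean 32 − 12 = 20, 48 per group. A two-proportion test with pooled null variance stands in for the logistic model. The proportion below cut c is Φ((c − mean)/18).

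| Cut | Control | Intervention | Power at 48 | n per group for 90% |
|---|---|---|---|---|
| 15 | 0.172 | 0.391 | 0.67 | 88 |
| 20 | 0.252 | 0.500 | 0.71 | 79 |
| 26 | 0.369 | 0.631 | 0.73 | 75 |
| 32 | 0.500 | 0.748 | 0.71 | 79 |
| 40 | 0.672 | 0.867 | 0.62 | 96 |

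A cross-check uses the asymptotic efficiency of a median split, 2/π = 0.637: 48 × 0.637 = 30.6, and Φ(12 / (18 × √(2/30.6)) − 1.96) = Φ(2.61 − 1.96) = 0.74. Together these give about 62-74%, against 90% for the comparison of means.

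**4. A separate illustration: pooling four visits as independent rows.** Assumptions: median split, and equal latent correlation ρ between visits. The binary correlation is φ = (2/π) × asin(ρ), the design effect is 1 + 3φ, and type I error = 2 × (1 − Φ(1.96/√(design effect))).

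| ρ | φ | Design effect | Type I error, formula | Type I error, simulation |
|---|---|---|---|---|
| 0.3 | 0.19 | 1.58 | 11.9% | 11.5% |
| 0.5 | 0.33 | 2.00 | 16.6% | 15.7% |
| 0.7 | 0.49 | 2.48 | 21.3% | 20.4% |

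The simulation used 20,000 runs per value of ρ with 48 per group. The range is about 12-21% instead of 5%.

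**The case against.** The best defence is that the same section already plans a sound test. If the scores are normal, the two groups are compared parametrically, and at one visit that is the comparison on which the 48 per group rests. A reader might infer from the logistic sentence that the plan contains no valid test of the 12-point difference. The documents do not support that, because the group comparison stands beside it. This part of the defence holds and limits the point to the longitudinal analysis and the undefined hierarchy.

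It can also be said that the scores need not be dichotomised, since logistic regression has an ordinal form and the WOMAC items are ordinal. The article does not name that form, so this does not rescue the sentence. It does mean that the power loss depends on a reading the text never states.

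The figures have limits too. The article says nothing about a median split or about pooling visits. The power loss (one visit) and the type I error (four pooled visits) belong to different analyses, so they must not be added together. A calculation on completers, 58 × 0.8 = 46 per group, would not match the planned carry-forward set either. With all 58 counted as full information, the median-split formula gives a fall from about 95% to about 82%. I use 48 because it is the plan's own figure.

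**Conclusion.** The sentence is wrong as written, and the point should be fixed before analysis. The one analysis tied to the repeated measures suits neither the 0-100 primary score nor the mean difference on which the trial is sized. The plan also does not say whether the group comparison or the logistic regression decides the trial, or at which visit.

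The mismatch with the sample size basis is firm, since 48 reproduces exactly as a comparison of means. The sizes in steps 3 and 4 are illustrations under assumed cut-points and correlations, not predictions of what the trial would do. Because a valid single-visit comparison is already planned, this does not leave the trial without a usable primary test.

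**What to change.** Replace the logistic regression sentence with the following:

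- **Model.** A linear mixed model for WOMAC physical function at 1, 3, 6 and 12 months, with group, visit, group-by-visit and baseline score as fixed effects and a within-patient covariance. Report between-group mean differences with 95% confidence intervals.
- **Primary contrast.** Name one for the 12-point hypothesis, either a single visit or the average over visits, and treat the other visits as secondary. A single-visit contrast keeps the existing sample size basis.
- **Missing data.** Fit the model to observed data and keep carry-forward only as a sensitivity analysis.
- **Baseline.** State that it is collected after randomisation in an un-blinded trial. Patients are randomised just before discharge; the baseline score is scheduled 3 days after discharge, before the first call on day 4. Add an analysis without baseline adjustment as a sensitivity check.
- **Other outcomes.** Use the same model for WOMAC pain and stiffness, SF-36 and self-efficacy. Keep logistic regression, as GEE or mixed-effects if repeated, only for binary outcomes defined in advance.

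The cost is wording, though more than one sentence, because carry-forward moves from the primary to a sensitivity analysis and a primary contrast must be chosen. No new data or patients are needed. The article reports enrolment at half the target, so the change could be made before any analysis.

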## Background

### Introduction

The number of primary total knee arthroplasty (TKA) procedures is increasing and estimated to 1.4 million worldwide in 2015 [1]. In Denmark approximately 9000 TKA procedures are performed annually [2]. The main clinical indication for TKA is osteoarthritis [3] causing severe pain and substantial functional disabilities, leading to a decrease in health-related quality of life [4].

TKA is a common procedure that, despite of low level of mortality and complications, entails a severe surgical trauma and a protracted recovery [5].

The implementation of the fast-track programs for surgical patients has reduced the stay in hospital for TKA-patients, and the length of stay is now only around 3 days in several Danish surgical centres [6]. Commonly the patients are discharged to home and referred to physiotherapy in the community settings, with only one scheduled follow-up by the surgeon 3 months post-surgery.

During the early rehabilitation period TKA- patients have experienced several health problems especially physical ones [7]. In a survey conducted at Gentofte University Hospital in 2011, 96% out of 86 patients identified 1–7 physical postoperative health problems two to three weeks after undergoing TKA (unpublished observations by the researcher responsible for this trial). The health-related information given during the admission course has been difficult to transfer to the home settings [8], and following discharge the patients have needed further guidance [9]. Although the problems were apparent, the patients were reluctant to contact health professionals due to a belief that their problems were too insignificant to bother health care providers with [10]. During the rehabilitation period the experience of inadequate preparation for physical symptoms and psychological reactions, as well as unrealistic expectations to activity level have led to anxiety, depression and disappointment [11] to the extent of affecting the patients´ general health [12].

Self-efficacy is the degree of belief of having adequate action-oriented resources to control events affecting the everyday life successfully [13]. Self-efficacy is positively correlated with physical and mental aspects of health [14]. Self-efficacy is an important parameter during the rehabilitation period following TKA [15-17] by influencing physical function and mental health [16].

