In non-pharmacological trials the care providers and the patients are frequently un-blinded [46]. The lack of blinding could affect the estimate of the treatment effect positively [47]. In this trial neither the patients nor the person conducting the consultations are blinded after the randomization, because it is impossible to hide whether the patients receive consultation or not. The participants who are assigned to receive a new treatment including extra follow-up may have favourable expectations, and those assigned to conventional treatment may be disappointed [48]. However, the patients have no previous experiences of the rehabilitation period after TKA and hereby no basis for comparison of any gain of the follow-up consultations with conventional treatment after being discharged following TKA. Furthermore, the control group has no knowledge of the content of the consultations, and contact between patients post discharge with opportunity to discuss benefits or disadvantages of follow-up consultations are unlikely. However, it cannot be excluded that the patients meet by chance at follow-up in the outpatient clinic.

Deviation from the protocol after randomization is expected, since some patients will withdraw, some may be unavailable at the times set for the consultations, and some may not return the questionnaires. Exclusion of the patients deviating from the protocol destroys the distribution of similar characteristics in the two groups and could influence the estimation of the effect of the intervention [49]. Intention to treat analysis will be performed including all randomized patients providing the least bias when comparing results between the two groups [50]. The drop-out rate can be expected to increase during the 12 months follow-up period and rapid response to unreturned questionnaires is executed by telephone calls to minimize the drop-out rate.

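### Carrying the last value forward as the primary intention-to-treat method conflicts with the recovery the protocol describes, and can bias later between-arm comparisons if drop-out is early or unequal or an early effect fades

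*Protocol article*

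**What the plan says.** The Outcome analysis section of the protocol article sets the analysis population: "All patients will be analysed in the groups to which they are randomly allocated according to intention to treat analysis". On missing outcomes it continues: "This analysis is primarily based on imputation of outcomes by carrying the last known outcome status forward". It adds that this "is supplemented by sensitivity analysis to examine the effect on the results", without naming a method.

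Other sections describe the data to which the rule will apply:

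- **Visits** (Outcome measures): "Outcome measures are collected at baseline defined by 3 days after discharge from hospital, and 1, 3, 6 and 12 months post-surgery". Table 1 admits only patients discharged within 4 days of surgery, so the first value that can be carried forward comes from about the first week.
- **Course** (Introduction): the operation "entails a severe surgical trauma and a protracted recovery".
- **Change in the primary scale** (WOMAC Index LK 3.1): "the mean changes at follow-ups 3 and 6 months post TKA-surgery were significant (p < 0.001) for all subscales". "The mean score of the subscale physical function 6 month post-surgery is estimated to 32", on a 0 to 100 scale where higher is worse.
- **Drop-out** (Sample size; Discussion): 20% is expected, and "The drop-out rate can be expected to increase during the 12 months follow-up period".
- **Timing of the effect** (Discussion): expected to be greatest in early recovery.
- **Blinding** (Discussion): none for patients, and controls may be disappointed with their allocation.

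**The concern.** Carrying the last value forward gives the right mean only if scores do not change after the last returned form. In a recovering population, a patient lost after the first form or the 1-month form enters a later comparison with a score that is on average too high, that is, too poor. If such patients are more numerous in one arm, or are lost earlier there, recovery that was never observed appears as a treatment difference. If the intervention helps early and the benefit then fades, carried values keep it alive at later visits even when drop-out is equal. The method also treats imputed scores as observed, so the standard error ignores the uncertainty of the imputation.

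The Discussion defends intention to treat as the least biased way to compare the groups. The chosen imputation works against that aim, and it determines the headline result. The choice is written down, so an unseen analysis plan does not explain it.

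**Working it through.** **The plan's own figure.** With a difference of 12, SD 18, two-sided α of 5% and power of 90%: n = 2 × [18 × (1.960 + 1.282) / 12]² = 47.3, rounded up to 48 per group, as stated. The 58 per group follows as 48 × 1.2 = 57.6. (Dividing by 0.8 would give 60; that is a separate matter.) With 58 complete patients per arm, power for 12 points is about 95%.

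**Formula.** With no true effect, the false difference at 12 months is

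Σ over visits of (share of controls last seen at visit v − share of intervention patients last seen at v) × (mean at v − mean at 12 months).

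If both arms share the same timing pattern, this becomes (difference in drop-out proportion) × (average excess of the carried values).

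**Inputs.** From the protocol: 6-month mean 32, SD 18, 58 per arm, 20% overall drop-out. Assumed: means of 60, 48, 38, 32 and 29 at baseline, 1, 3, 6 and 12 months; within-patient correlation 0.6; the imbalance and timing of drop-out; and 12 months as the visit compared. The excesses over the 12-month mean are 31, 19, 9 and 3.

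**Average excess by timing of the last form (baseline / 1 / 3 / 6 months)**

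- Even, 25% each: (31 + 19 + 9 + 3) / 4 = 15.5
- Later, 10/20/30/40%: 3.1 + 3.8 + 2.7 + 1.2 = 10.8
- All last seen at 6 months: 3

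**No true effect** (type I error from simulated two-sample t-tests)

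| Timing | 10% intervention v 30% control | 15% v 25% | 20% v 20% |
|---|---|---|---|
| Even | 0.20 × 15.5 = 3.1 points; about 13.5% | 1.6 points; 6 to 7% | 0; about 5% |
| Later | 0.20 × 10.8 = 2.2 points; about 9.5% | 1.1 points; about 6.5% | 0; about 5% |
| All at 6 months | 0.20 × 3 = 0.6 points; 5 to 6% | 0.3 points; about 5% | 0; about 5% |

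**Other recovery curves, 10% v 30%**

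- Steep curve (65, 50, 36, 32, 28), early drop-out (50/30/10/10%): excess 18.5 + 6.6 + 0.8 + 0.4 = 26.3; 0.20 × 26.3 = 5.3 points, type I error about 26%.
- Mild curve (45, 40, 35, 32, 30), late drop-out (10/10/30/50%): excess 5.0; 1.0 point, about 6%.
- Limiting case, steep curve with only the baseline form from every drop-out: 0.20 × 37 = 7.4 points.

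**Early effect that fades** (0, 12, 9, 4 and 0 points at the five visits; main curve)

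- Equal 20% drop-out, even timing: 0.20 × (0 + 12 + 9 + 4) / 4 = 1.25 points at 12 months, where the truth is zero. Later timing gives 1.3, all at 6 months 0.8. The null hypothesis is rejected in about 6% of trials.
- 15% v 25%, even timing: 0.25 × 15.5 − 0.15 × (15.5 − 6.25) = 2.5 points, with rejection in about 9 to 11%.

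**Bias in the other direction** (constant 12 points from month 1; 30% intervention v 10% control)

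- Even timing: control mean 29 + 0.10 × 15.5 = 30.55. Intervention means are 60, 36, 26, 20 and 17, so the carried average is 35.5 and the arm mean is 17 + 0.30 × (35.5 − 17) = 22.55. The estimate is 8.0 in place of 12, and power is about 56%.
- Later timing: about 9.5 points and 75% power.
- Equal 20% drop-out: about 11.4 to 12.0 points, with power of about 85 to 94% depending on timing.

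**The case against.** The strongest objections concern size, and much of them stands.

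- **Not every drop-out is held at an early score.** A reader might infer so. It is true only of patients lost after the baseline or 1-month form. The protocol expects drop-out to build up over the year and plans a telephone reminder for late questionnaires. Later losses carry values nearer the plateau, and the bias shrinks to about half a point if all are last seen at 6 months.
- **The 15.5-point excess does not outweigh the 12-point target.** It is a deviation per drop-out within one arm, whereas 12 is a difference between arms. At 20% drop-out it moves an arm mean by about 3 points, and it cancels under the null when drop-out is equal in amount and timing. No scenario produced a false 12-point difference.
- **The protocol does not say that the changes are large.** It reports significance at 3 and 6 months, with no size and no starting point. The baseline means used above are assumptions.
- **Nor does it say that controls will return fewer forms.** It raises disappointment and then argues that patients have no earlier experience for comparison. A 20-point imbalance is an illustration, not a forecast.
- **The 12-month contrast is assumed.** The Primary outcome section speaks of a 12-month period without naming a visit. An earlier comparison would carry fewer values forward.
- **A sensitivity analysis is planned.** An article may leave its method to a fuller document. That softens the problem but does not remove it, because the headline result still comes from the carried values.

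None of this supplies a reason why a score from early recovery should represent a patient months later.

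**Conclusion.** The point holds, and it should be fixed. The carry-forward rule assumes constant scores, while the protocol describes changing ones and an effect concentrated early. The mechanism follows from the protocol's own statements; the size does not, because only the 6-month mean, the SD, the arm size and the overall drop-out are given.

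On the main assumed curve with no true effect, 10% v 30% drop-out gives a false difference of about 0.5 to 3 points and a type I error of about 5% to 13.5%. At 15% v 25% the range is about 0.3 to 1.6 points and 5% to 7%. A steeper curve with early drop-out reaches about 5 points. Equal drop-out gives no bias under the null, and about 1 point if an early effect has faded by 12 months. The direction depends on which arm loses more patients or loses them earlier. The documents do not support the view that this method alone could create the 12-point target difference, or that it must favour the intervention.

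**What to change.** By dated amendment, before any data are compared by arm:

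1. Make the primary analysis a likelihood-based linear mixed model for repeated measures on all observed visits of all randomised patients, as allocated, valid under missing at random and without single imputation. Multiple imputation is an acceptable alternative.
2. Keep carry-forward, if at all, only as a labelled sensitivity analysis.
3. Specify a sensitivity analysis for data not missing at random, for example multiple imputation with drop-outs in the intervention arm shifted to worse scores.

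The planned visits already supply the data, so no patients, forms or visits are added. The article reports half the intended patients enrolled, which leaves time to make the change before results are seen. The cost is some extra analysis work and reliance on the missing-at-random assumption, which the third item is there to test.
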